### Randomization, Allocation Concealment, and Blinding

Eligible patients with RA were enrolled and assigned to 4 treatment groups using block randomization with a 1:1:1:1 allocation ratio. Statistical experts who were not involved in the study or data analysis generated the block randomization sequence using the SAS software.

This is an open-label study; therefore, neither researchers nor participants were blinded. Only adjudicators of outcome measures and statistical analysts were blinded to group allocation.

### Interventions

All participants received targeted TGT-based therapy, administered either as monotherapy or in combination with methotrexate (10‐15 mg/wk), leflunomide (10‐20 mg/d), or hydroxychloroquine (200‐400 mg/d). Participants were evaluated at baseline and then every 4 weeks for a total of 12 weeks.

For ethical reasons, nonsteroidal anti-inflammatory drugs (NSAIDs), such as diclofenac sodium enteric-coated tablets, were permitted as rescue therapy when pain became intolerable during the study. The permitted regimen was 25 mg orally 3 times daily before meals, and the use, dosage, and therapeutic effects were recorded in detail.

However, during the trial period, all other medications with similar mechanisms or effects to the study drug were prohibited, except for rescue therapy for intolerable RA pain. This included glucocorticoids (eg, prednisone acetate and methylprednisolone), biologic agents (eg, adalimumab and secukinumab), and other disease-modifying antirheumatic drugs (eg, cyclophosphamide and cyclosporine).

### Outcome Measures

#### Primary Outcome Measurement

The American College of Rheumatology 20% improvement (ACR20) response rate at week 12 is defined as ≥20% improvement in both tender joint count (TJC) and swollen joint count (SJC), as well as ≥20% improvement in at least 3 of the following 5 domains: patient global assessment (PGA), medical doctor global assessment (MDGA), patient pain visual analog scale (VAS), Health Assessment Questionnaire Disability Index (HAQ-DI), and acute-phase reactants (erythrocyte sedimentation rate [ESR] or C-reactive protein [CRP]).

#### Secondary Outcome Measurement

##### Overview

The secondary outcome measures included Disease Activity Score-28 (DAS28) using ESR (DAS28-ESR) and DAS28 using CRP (DAS28-CRP) response rates, Clinical Disease Activity Index (CDAI), Simplified Disease Activity Index (SDAI), pain VAS score (0 to 10), PGA, MDGA, quality of life (36-Item Short Form Health Survey [SF-36]), HAQ-DI, and inflammatory factor levels. The incidence of adverse events was measured using Common Terminology Criteria for Adverse Events (CTCAE), version 5.0. The measurement of each outcome and the schedule of visits are shown in Table 1. Participants were reminded to complete these diaries via text message, phone call, email, and instant messaging (WeChat; Tencent Holdings Ltd).

**Table 1. T1:** Visit schedule and assessments.

Variables	Registration (visit 0)	Baseline (visit 1, day 0)	Week 4 (visit 2, days 25-31)	Week 8 (visit 3, days 49-63)	Week 12 (visit 4, days 74-94)
Enrollment					
Eligibility screen	✓				
Baseline demographic		✓			
Clinical characteristics		✓			
Informed consent		✓			
Randomization		✓			
Interventions					
Group 1: TGT^a^ monotherapy		✓	✓	✓	✓
Group 2: TGTs+methotrexate		✓	✓	✓	✓
Group 3: TGTs+hydroxychloroquine		✓	✓	✓	✓
Group 4: TGTs+leflunomide		✓	✓	✓	✓
Assessments					
Primary outcome: ACR20^b^ response rate			✓	✓	✓
Secondary outcome					
DAS28-ESR^c^		✓	✓	✓	✓
DAS28-CRP^d^		✓	✓	✓	✓
CDAI^e^		✓	✓	✓	✓
SDAI^f^		✓	✓	✓	✓
Pain VAS^g^		✓	✓	✓	✓
PGA^h^		✓	✓	✓	✓
MDGA^i^		✓	✓	✓	✓
Quality of life (SF-36^j^)		✓	✓	✓	✓
HAQ-DI^k^		✓	✓	✓	✓
Inflammatory factors		✓	✓	✓	✓
Safety monitoring					
Adverse events		✓	✓	✓	✓
Research completion					✓

a TGT: Tripterygium glycoside tablet.

b ASR20: American College of Rheumatology 20% improvement.

c DAS28-ESR: Disease Activity Score-28 using erythrocyte sedimentation rate.

d DAS28-CRP: Disease Activity Score-28 using C-reactive protein.

e CDAI: Clinical Disease Activity Index.

f SDAI: Simplified Disease Activity Index.

g VAS: visual analog scale.

h PGA: patient global assessment.

i MDGA: medical doctor global assessment.

j SF-36: 36-Item Short Form Health Survey.

k HAQ-DI: Health Assessment Questionnaire Disability Index.

##### DAS28-ESR and DAS28-CRP Response Rates

DAS28-ESR and DAS28-CRP response rates were used to determine RA disease activity, including the number of swollen joints (SJC; 0 to 28), the number of tender joints (TJC; 0 to 28), the PGA (VAS; 0 to 10), the ESR (mm/h), and the CRP (mg/L) level. The DAS28 activity rate was low (DAS28 ≤3.2). According to the European Alliance of Associations for Rheumatology (EULAR) response criteria, a change in DAS28 from baseline of >1.2 indicates an excellent response, a change of ≥0.6 to ≤1.2 indicates a moderate response, and a change of ≤0.6 indicates no response [22].

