##### Clinical Disease Activity Index

The CDAI was calculated using the following formula: CDAI = TJC + SJC + PGA + MDGA. The scoring criteria are as follows: ≤2.8 indicates clinical remission, >2.8 to ≤10.0 indicates low disease activity, >10.0 to <22.0 indicates moderate disease activity, and >22 indicates high disease activity [23].

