##### Simplified Disease Activity Index

The SDAI is an extended version of the CDAI that includes CRP. It is calculated using the following formula: SDAI = TJC + SJC + PGA + MDGA + CRP (mg/dL). The scoring criteria are as follows: ≤3.3 indicates clinical remission, >3.3 to ≤11.0 indicates low disease activity, >11.0 to ≤26.0 indicates moderate disease activity, and >26.0 indicates high disease activity [24].

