### Statistical Analysis

The primary outcome—the ACR20 response rate at week 12—will be compared between each combination therapy group and the TGT monotherapy group using logistic regression. The study center will be included as a fixed effect to account for potential site differences.

Secondary outcomes (eg, DAS28-ESR and CDAI) will be analyzed using mixed-effects models for repeated measures. These models will include fixed effects for treatment, visit, treatment-by-visit interaction, baseline value, and study center, with participants included as a random intercept.

All primary analyses will be conducted on the intention-to-treat population, defined as all randomized participants who received at least 1 dose of the study drug. Missing data will be handled using multiple imputation under the missing-at-random assumption, generating 20 imputed datasets. Sensitivity analyses will be performed to evaluate the robustness of conclusions under different missing data assumptions.

Safety data, including adverse events, will be summarized descriptively by treatment group. Between-group comparisons of adverse event rates will be conducted using the Fisher exact test.

Rescue therapy with NSAIDs was permitted for intolerable joint pain, in line with ethical requirements and standard clinical practice for the management of RA. As pain and swelling are universal symptoms of active RA, the requirement for rescue analgesia reflects real-world treatment conditions and will not be statistically adjusted in the primary analysis. The use of rescue medication will be documented descriptively and reported by treatment group. If notable between-group differences in the frequency of rescue therapy are observed, exploratory sensitivity analyses will be conducted to assess their potential influence on efficacy outcomes.

All analyses will be performed using SAS (version 9.4) and R (version 4.4.s2; R Foundation for Statistical Computing). Between-group differences will be reported with 95% CIs. Statistical significance is set at α=.05 (2-sided).

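### A DAS28 change of 0.6 falls in two response grades, CDAI 22.0 falls in none, no DAS28 responder is defined, and the secondary model, written for scores, rests on a random intercept alone

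*Protocol article*

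**What the plan says.** **DAS28 grades** (DAS28-ESR and DAS28-CRP Response Rates). The top grade is defined by "a change in DAS28 from baseline of >1.2 indicates an excellent response". For the other two, "a change of ≥0.6 to ≤1.2 indicates a moderate response, and a change of ≤0.6 indicates no response". The same paragraph also describes a DAS28 of 3.2 or below as low activity.

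**CDAI bands** (Clinical Disease Activity Index). The lower bands are "≤2.8 indicates clinical remission, >2.8 to ≤10.0 indicates low disease activity". The upper bands are ">10.0 to <22.0 indicates moderate disease activity, and >22 indicates high disease activity".

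**SDAI bands** (Simplified Disease Activity Index), for comparison: ">11.0 to ≤26.0 indicates moderate disease activity, and >26.0 indicates high disease activity".

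**Outcome name.** The Abstract, the Overview of secondary outcomes and the DAS28 section heading all call the DAS28 outcomes response rates; the Overview has "DAS28 using CRP (DAS28-CRP) response rates". Table 1 lists DAS28-ESR and DAS28-CRP without that term and has them measured at baseline.

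**Model** (Statistical Analysis). "Secondary outcomes (eg, DAS28-ESR and CDAI) will be analyzed using mixed-effects models for repeated measures". The fixed effects are treatment, visit, their interaction, baseline value and centre, "with participants included as a random intercept". No link function and no residual covariance are stated. Logistic regression is named only for ACR20.

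**The concern.** Four things need settling before anyone can program the secondary efficacy analysis.

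1. The DAS28 grades overlap at 0.6. If moderate response counts as response, this is the line between responder and non-responder.
2. The CDAI bands have a hole at 22.0. CDAI adds two joint counts and two 0 to 10 scores, so 22 is an attainable value.
3. A rate needs a yes/no definition, and the text offers several candidates without choosing. The model has a baseline-value term and takes CDAI as a companion example, which fits a score. A response defined by change from baseline has no baseline value of its own.
4. For continuous scores, a random intercept with independent, equal-variance residuals implies the same variance at weeks 4, 8 and 12 and the same correlation between any two visits. If the spread of scores changes during follow-up, the standard error of a week-12 contrast is wrong.

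The trial is open-label. Data collection is complete, and the Abstract says that analyses have not been performed. If these choices stay open, a responder definition or boundary could be settled after results are seen.

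**Working it through.** The plan gives no figure of its own on this point, so there is none to reproduce.

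**Step 1. Do the categories partition the scale?** The published limits were coded exactly and every value on a 0.01 grid was tested for membership.

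| Measure | Rules as written | Values not in exactly one category |
|---|---|---|
| DAS28 change | >1.2; 0.6 to 1.2, both ends included; ≤0.6 | 0.60 (in two) |
| CDAI | ≤2.8; >2.8 to ≤10.0; >10.0 to <22.0; >22 | 22.00 (in none) |
| SDAI | ≤3.3; >3.3 to ≤11.0; >11.0 to ≤26.0; >26.0 | none |

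Making one of the two 0.6 limits strict, and giving 22.0 to one CDAI category, leaves every grid value in exactly one category.

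**Step 2. How many patients could sit on a boundary?** The documents give no means or SDs, so normal distributions are assumed. The share recorded at value v with rounding half-width h is Φ((v+h−m)/s) − Φ((v−h−m)/s), multiplied by the 181 enrolled (Results).

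- DAS28 change at 0.6, with mean m from 0.6 to 1.5 and SD s from 0.8 to 1.2:
  - One decimal (h = 0.05): from 0.0251 (m = 1.5, s = 1.2) to 0.0498 (m = 0.6, s = 0.8). 181 × 0.0251 = 4.5 and 181 × 0.0498 = 9.0 patients.
  - Two decimals (h = 0.005): 0.0025 to 0.0050, or 0.5 to 0.9 patients.
- CDAI at 22, with m from 12 to 22 and s from 6 to 10:
  - Whole numbers (h = 0.5): 0.0166 to 0.0664, or 3.0 to 12.0 patients.
  - Steps of 0.1 (h = 0.05): 0.0017 to 0.0066, or 0.3 to 1.2 patients.

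**Step 3. Outcome against model.** The DAS28 section supports at least three binary definitions: top grade only; top or moderate grade; DAS28 of 3.2 or below at the visit. None is chosen. The Statistical Analysis section pairs DAS28-ESR with CDAI in one model that has a baseline term. Table 1, which has a DAS28 value at baseline, agrees with a score; the Abstract, Overview and section heading say rate.

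**Step 4. What the random intercept does to a week-12 contrast.** With complete data, independent equal-variance residuals and a treatment-by-visit mean, the model's variance at every visit is the average of the three visit variances. A nominal 5% two-sided test at week 12 then has size 2 × [1 − Φ(1.96 × √(average variance / week-12 variance))] in large samples.

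| Assumed SDs, weeks 4/8/12 | Average variance | Week-12 variance | Ratio | 1.96 × √ratio | Size |
|---|---|---|---|---|---|
| 1.0/1.0/1.0 | 1.000 | 1.00 | 1.000 | 1.960 | 5.0% |
| 0.9/1.0/1.1 | 1.007 | 1.21 | 0.832 | 1.788 | 7.4% |
| 0.8/1.0/1.2 | 1.027 | 1.44 | 0.713 | 1.655 | 9.8% |
| 1.2/1.0/0.8 | 1.027 | 0.64 | 1.604 | 2.482 | 1.3% |

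For example, in the third row (0.64 + 1.00 + 1.44)/3 = 1.027 and 1.027/1.44 = 0.713.

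A simulation agrees. It used 20,000 trials per pattern, 42 per arm, AR(1) correlation 0.6 and no treatment effect. The variance pooled over visits gave 0.051, 0.070, 0.100 and 0.012 in the same order; the week-12 variance gave 0.048 to 0.054.

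**The case against.** **The boundaries are slips with little effect.** This largely stands. At two decimals about one patient or fewer is at 0.60, and the documents state no rounding to one decimal. CDAI itself is the listed and modelled outcome, so the gap bites only where CDAI categories are reported. But the 0.6 rule defines a named secondary outcome, and both faults are wrong as written.

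**A worsening above 1.2 might be read as an excellent response, because change has no stated direction.** A reader might infer this, but the documents do not support it. The rule grades response under named response criteria, so improvement is plainly meant.

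**The stated model cannot analyse a response rate.** This is also tempting and goes too far. The text never says the model is linear, and a random-intercept model with a logit link is a standard analysis of repeated binary data. The link function may be left to an analysis plan that is not shown. Baseline DAS28 could also serve as the covariate. What remains is that outcome name and model wording do not match, and that no responder is defined.

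**The covariance point is a preference resting on assumed SDs.** In part this stands. The article states no residual covariance, and one richer than independence would remove the restriction. It does not name a week-12 contrast as the secondary estimate. The simulation describes no baseline covariate, centre or missing data, and it uses 42 per arm although 181 were enrolled. The assumed patterns err in both directions. It would be wrong to infer that the trial's secondary error rates are inflated; the documents show only that a random intercept alone is exposed if variances differ by visit.

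**Conclusion.** The overlap at a DAS28 change of 0.6 and the gap at CDAI 22.0 are certain from the text and confined to those single values. The missing DAS28 responder definition is the more consequential ambiguity, because it decides who counts as a responder across the scale; the model wording needs to be reconciled with it.

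The covariance point is a worthwhile improvement whose need cannot be measured from the documents. The range of about 1% to 10% for a nominal 5% test rests on the assumed SD patterns, complete data and independent residuals. With equal SDs there is no distortion. Both size and direction for this trial are unknown.

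The primary ACR20 analysis and the sample size do not depend on any of this. The matter should be settled before analysis, but it does not threaten the trial's main conclusion.

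**What to change.** Before the analysis starts:

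1. Make one of the two 0.6 limits strict, checking which against the response criteria that the article cites.
2. Assign CDAI 22.0 to one category, for example by closing the moderate band at 22.0 in the way the SDAI rule closes its own at 26.0.
3. Define a binary DAS28 responder, saying which grades count and what part, if any, the 3.2 threshold plays. Analyse it at week 12 by logistic regression with centre and baseline DAS28.
4. Reserve the repeated-measures model for the continuous DAS28, CDAI, SDAI and other scores, and say so.
5. In that model, replace the random intercept with an unstructured within-patient covariance and use Kenward-Roger degrees of freedom.

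The cost is wording and model code. Three visits need 3 variances and 3 covariances, 6 parameters in all, which 181 patients can support. The small downside is estimating these in place of the random-intercept model's 2 variances.

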##### Clinical Disease Activity Index

The CDAI was calculated using the following formula: CDAI = TJC + SJC + PGA + MDGA. The scoring criteria are as follows: ≤2.8 indicates clinical remission, >2.8 to ≤10.0 indicates low disease activity, >10.0 to <22.0 indicates moderate disease activity, and >22 indicates high disease activity [23].

##### Simplified Disease Activity Index

The SDAI is an extended version of the CDAI that includes CRP. It is calculated using the following formula: SDAI = TJC + SJC + PGA + MDGA + CRP (mg/dL). The scoring criteria are as follows: ≤3.3 indicates clinical remission, >3.3 to ≤11.0 indicates low disease activity, >11.0 to ≤26.0 indicates moderate disease activity, and >26.0 indicates high disease activity [24].

##### Pain VAS Score

The VAS is a tool in which patients rate the intensity of their pain on a straight line ranging from 0 to 10 points. A score of 0 represents “no pain,” and a score of 10 represents “very severe pain.” The VAS reflects the subjective pain level of patients with RA and is often used to compare pain levels before and after treatment.

##### Patient Global Assessment

The PGA is an overall score (0 to 10) based on the patient’s subjective perception of their disease activity. It reflects the patient’s perception of the effect of treatment and is based on feelings of pain, fatigue, and functional limitations.

##### Medical Doctor Global Assessment

The MDGA is an overall score ranging from 0 to 10 based on the physician’s evaluation of the patient’s current disease activity. The score reflects the clinician’s judgment of the inflammatory burden and incorporates findings from the patient’s physical examination (eg, joint swelling and tenderness), laboratory results, and functional observations.

##### Quality of Life Assessment (SF-36)

The SF-36 covers 8 dimensions, such as physical function and social function, with a total of 36 items. Each dimension was standardized to a score of 0 to 100, and the total score reflected the overall quality of life. The long-term impact of RA on several dimensions of life was assessed.

##### Health Assessment Questionnaire

The HAQ-DI is a tool used to assess activities of daily living in individuals with RA. It contains 20 questions covering activities such as dressing, eating, and walking, reflecting the actual impact of the disease on daily life. The HAQ-DI is scored from 0 to 3, with 0 indicating no difficulty and 3 indicating inability to complete the activity. Higher total scores indicate more severe functional limitations.

##### Detection of Inflammatory Factors

These factors include tumor necrosis factor-α (TNF-α) and interleukin-6 (IL-6). TNF-α, a proinflammatory cytokine, can be detected using an enzyme-linked immunosorbent assay. Elevated levels of TNF-α indicate active inflammation. IL-6 mediates the acute-phase response and is associated with joint destruction. IL-6 is detected by the same methodology as TNF-α.

### Incidence of Adverse Events

Safety will be evaluated through routine blood tests, as well as renal and hepatic function tests.

Drug-related adverse events, including infections, liver dysfunction, kidney dysfunction, and treatment-related complications (eg, injection site reactions), were recorded. Serious adverse events were documented separately. Adverse events will be summarized by frequency (eg, number and percentage of participants affected) and severity according to the CTCAE criteria.

### Patients’ Compliance Assessment

Patients’ adherence was assessed by counting the number of remaining cartridges at the end of treatment. In addition, dropout status and reasons for discontinuation were recorded throughout the 12-week observation period.

### Patients and Public Involvement

Patients and the public were not involved in the development of the research question or study design. They will not participate in trial recruitment, conduct, or reporting of results. Trial results will be disseminated to participants via social media.

### Sample Size

The sample size was calculated for a multicenter RCT with 1 common control group (TGT monotherapy) and 3 active treatment groups (TGTs+methotrexate, TGTs+hydroxychloroquine, and TGTs+leflunomide). The primary hypothesis is that each combination therapy will be superior to TGTs monotherapy for the ACR20 response rate at week 12. The assumed ACR20 response rates were derived from an unpublished study conducted at our center in 2022 ([name], unpublished data, May 2022). This study included 30 patients with moderate RA (DAS28 3.2-5.1), randomized 1:1 to receive either TGT monotherapy (n=15) or TGTs+methotrexate (n=15) for 12 weeks. The observed ACR20 response rates were 53.3% (8/15) in the monotherapy group and 80% (12/15) in the combination group. On the basis of these data, the following assumptions were made:

TGT monotherapy—ACR20 response rate=54%

Combination therapy (TGTs+methotrexate, TGTs+hydroxychloroquine, and TGTs+leflunomide)—ACR20 response rate=80%

We consider this absolute difference of 26 percentage points to be clinically meaningful.

The sample size calculation was performed using PASS (Power Analysis and Sample Size) software (version 15; NCSS, LLC). The procedure selected was “chi-square tests” to compare multiple treatment groups with a common control while controlling the family-wise type I error rate.

Input parameters included the following: solving for sample size, degree of freedom 3; power 0.8; α=.05, and effect size (w=0.255098).

Consequently, the Dunnett procedure required 42 participants per group, resulting in a total sample size of 168 before accounting for dropouts. With an estimated dropout rate of 10%, the adjusted total sample size was approximately 188 participants, corresponding to approximately 47 participants per group.

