**Methods:**

This multicenter, open-label randomized controlled trial recruited 188 participants (47 per group) from 3 hospitals. Eligible patients were stratified by study center and randomized in a 1:1:1:1 ratio to receive TGT monotherapy, TGT plus methotrexate, TGT plus leflunomide, or TGT plus hydroxychloroquine. The primary outcome was the American College of Rheumatology 20% improvement response rate. Secondary outcome measures included the Disease Activity Score-28 (DAS28) using erythrocyte sedimentation rate and DAS28 using C-reactive protein response rates, the Clinical Disease Activity Index, the Simplified Disease Activity Index, the pain visual analog scale (0 to 10 points), the patient global assessment, the medical doctor global assessment, quality of life (36-Item Short Form Health Survey), and the Health Assessment Questionnaire Disability Index. All enrolled patients were followed up every 4 weeks for a total of 12 weeks. Adverse events were recorded during the observation period of the study. All patients randomized in this study will be included in the intention-to-treat analysis.

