**Results:**

This study was funded in February 2024. Funding was provided by the Beijing Tongzhou District Science and Technology Planning Project. Recruitment of participants commenced on September 1, 2024, and concluded on December 31, 2025. A total of 181 patients were enrolled. Final data collection has been completed, and data cleaning is currently underway. Statistical analyses have not yet been performed. The primary results are expected to be submitted for publication by the end of 2026.

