## Discussion

### Summary of Anticipated Findings

This trial is expected to provide robust evidence on the comparative efficacy and safety of TGT-based combination therapies in patients with moderately active RA. We hypothesize that all 3 TGT combination regimens (TGTs+methotrexate, TGTs+hydroxychloroquine, and TGTs+leflunomide) will result in significantly higher ACR20 response rates at week 12 than TGT monotherapy. These findings are expected to clarify the risk-benefit profile of these combinations and identify which regimen offers the most favorable balance of efficacy and tolerability for different patient subgroups.

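### The 42 per group comes from a 3-df omnibus chi-square test, not Dunnett, so the 80% power does not apply to the hypothesis that each combination beats monotherapy

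*Protocol article*

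**What the plan says.** The Sample Size section of the protocol article sets the objective as pairwise: "The primary hypothesis is that each combination therapy will be superior to TGTs monotherapy for the ACR20 response rate at week 12". It assumes "TGT monotherapy—ACR20 response rate=54" (percent) and "Combination therapy (TGTs+methotrexate, TGTs+hydroxychloroquine, and TGTs+leflunomide)—ACR20 response rate=80" (percent). It reports using the chi-square procedure in PASS, describes that procedure as comparing several groups with a common control under family-wise error control, and lists the inputs as "solving for sample size, degree of freedom 3; power 0.8", α=.05 and w=0.255098. It then concludes: "Consequently, the Dunnett procedure required 42 participants per group, resulting in a total sample size of 168 before accounting for dropouts". A 10% dropout allowance brings the total to about 188, or 47 per group.

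The Statistical Analysis section compares each combination with monotherapy by logistic regression, with centre as a fixed effect, at two-sided α=.05. It describes no omnibus test and names no multiplicity adjustment. The Discussion (Summary of Anticipated Findings) repeats the pairwise aim for all three regimens, which it expects "will result in significantly higher ACR20 response rates at week 12 than TGT monotherapy".

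On numbers, the Methods part of the abstract says the trial "recruited 188 participants (47 per group) from 3 hospitals", while its Results part says: "A total of 181 patients were enrolled".

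**The concern.** Three degrees of freedom is what a 4×2 table gives for a test of overall homogeneity. Rejecting that hypothesis says the four arms are not all alike. It does not say which combination, if any, beats monotherapy, and it controls no error rate across the three comparisons. A Dunnett calculation would instead need a critical value for three correlated comparisons with a shared control.

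If the 42 is an omnibus figure, the 80% answers a question the trial does not ask, and the trial has no correct power statement for its primary hypothesis. This matters for interpretation. The trial is meant to identify the best combination, and a reader who trusts 80% power per comparison may read too much into a regimen that misses significance.

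**Working it through.** **Inputs.** From Sample Size: control rate 0.54, each combination 0.80, df 3, α 0.05, power 0.80, w=0.255098, dropout 10%. From Statistical Analysis: two-sided 0.05, each combination against monotherapy. From Study Design: 1:1:1:1 allocation. From Results: 181 enrolled, so 181/4 ≈ 45 per arm.

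**1. Reproduce the plan's figure.**
- Mean rate = (0.54 + 3×0.80)/4 = 0.735.
- Mean squared deviation = (0.195² + 3×0.065²)/4 = 0.0507/4 = 0.012675.
- w = √[0.012675/(0.735×0.265)] = √0.065075 = 0.255098, exactly the stated input.
- Power of the 3-df chi-square test, with noncentrality N·w²: N=167 gives 0.7986 and N=168 gives 0.8012. The smallest N reaching 80% is therefore 168, or 42 per group.
- Dropout: 42/0.9 = 46.7, rounded up to 47; 4×47 = 188.

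Every stated number is recovered from the omnibus test.

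**2. Dunnett critical value.** For three comparisons with a common control and equal arms (correlation 0.5), the large-sample two-sided 5% value is 2.349, a per-comparison α of 0.0188.

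**3. Pairwise power by normal approximation.** With d=0.26, mean rate 0.67, √(2×0.67×0.33)=0.665 and √(0.54×0.46+0.80×0.20)=0.639:

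power = Φ[(0.26√n − c×0.665)/0.639]

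- n=42, c=1.96: Φ[(1.685−1.303)/0.639] = 0.725
- n=42, c=2.349: Φ[(1.685−1.562)/0.639] = 0.576
- n=45, c=2.349: Φ[(1.744−1.562)/0.639] = 0.612

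**4. Joint power by binomial simulation (pooled z).** The per-comparison results are 1 to 2 points above the approximation.

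| Method (two-sided) | n per arm | Each comparison | All three | At least one |
|---|---|---|---|---|
| Single-step Dunnett | 42 | 59% | 34% | 82% |
| Single-step Dunnett | 45 | 62% | 39% | 84% |
| Step-down Dunnett | 42 | 66% | 51% | 82% |
| Step-down Dunnett | 45 | 69% | 54% | 84% (first step is the single-step test) |
| Unadjusted 0.05 | 42 | 73% | 53% | 91% |
| Unadjusted 0.05 | 45 | 77% | 57% | 93% |

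**5. Size needed for 80% per comparison.** n = [c×0.665 + 0.842×0.639]²/0.26².
- Unadjusted two-sided: 51 per arm.
- Two-sided Dunnett: 66 per arm.
- One-sided Dunnett: 54 per arm.

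Only an unadjusted one-sided 0.05 test (40 per arm) comes near 42, and it contradicts both the two-sided α and the claimed family-wise control.

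**The case against.** The strongest reply accepts the mislabel and disputes its size. The article names Dunnett without saying single-step or step-down, and its Statistical Analysis section names no adjustment. Step-down Dunnett has the same family-wise control and does better: 66% per comparison and 51% for all three at 42 per arm. The lowest figures therefore belong to one variant. This stands, and any restated power must name its method. It does not rescue the claim, because even the unadjusted analysis falls short of 80% for each comparison.

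Second, the text says only that power is 0.8, and at-least-one power under Dunnett is about 82%. That is true, but the stated objective is each combination and the listed inputs are not those of an at-least-one calculation. The agreement is a coincidence.

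Third, the plan already promises 95% confidence intervals and recruitment is over, so nothing in the conduct changes. That limits the remedy to text. It does not make the power statement right.

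Fourth, 188 versus 181 is a separate wording matter, and the same abstract gives 181. Agreed that it is secondary, but the two statements conflict. The loss of omnibus power (78.8% at 163, that is, 181 less 10%) is too small to matter, and missing outcomes are to be multiply imputed.

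**Conclusion.** The concern holds. The 42 per group is exactly the 3-df omnibus result, and attributing it to Dunnett is wrong. The 80% does not apply to the hypothesis that each combination is superior. With 42 to 45 per arm, power per comparison is about 59–62% under two-sided single-step Dunnett, 66–69% under step-down Dunnett and 73–77% with no adjustment. Power for all three is about 34–39%, 51–54% and 53–57% respectively. Under the single-step version, a true 26-point benefit in a given arm would be missed about 4 times in 10.

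These figures assume the plan's own rates of 54% and 80%, equal arms, and a two-sample comparison of proportions in place of the centre-adjusted logistic model. The 45-per-arm figures assume no loss from the 181 enrolled.

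**What to change.** Correct the Sample Size section without enrolling more patients:

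1. State that 168 gives 80% power for the 3-df omnibus chi-square test only. Delete the claims that the Dunnett procedure required 42 and that the chi-square procedure controlled family-wise error against a common control.
2. State which multiplicity method, if any, applies to the three comparisons, and make Sample Size and Statistical Analysis agree on it.
3. Report power for those comparisons at the 181 enrolled, under the method named. For single-step two-sided Dunnett this is about 60% per comparison, 34–39% for all three and 82–84% for at least one, depending on losses. For another method, use the corresponding rows of the table.
4. Preferably, add that a non-significant arm will be read from its confidence interval and not as absence of benefit.
5. Change the abstract to 188 planned and 181 enrolled.

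The cost is a text correction and a less favourable stated power. The article says analyses have not yet been performed, so the correction can still be made before results are known.
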